In each module, participants receive new information and are introduced to new at-home exercises to be completed between modules. Self-exploration (Modules 2-4) and sensate focus exercises (Modules 6-8) as well as information on the prevalence of sexual dysfunctions, genital anatomy, and sexual response (Modules 1-3) are included in both COPE and MIND. In Module 2, participants will be introduced to the circular sexual response model as proposed by Basson [39] and in each of the following modules, different parts of the cycle will be presented. This model proposes that women with low desire tend to enter sexual situations from a state of neutrality and, if context and stimulation are adequate, may develop sexual arousal and responsive sexual desire during the course of a (pleasing) sexual encounter. (For more information, see Basson [40]). Participants are given the opportunity to work with their sexual response cycle, to reflect on their own situation (eg, to identify contexts they find sexually arousing, to explore reasons for sexual activity), and to develop strategies to improve their sexual experiences.

**Table 1 table1:** Content of the modules.

Module	Content		
	MIND	COPE	Sex therapy (for both interventions)
1	Introduction to mindfulness	Introduction to cognitive behavioral model and body image	Psychoeducation, information about psychological and physiological aspects of sexual response
2	Being present in the moment: Formal and informal mindfulness	Sexual myths	Self-exploration, body exposure
3	Bodily sensations, sitting meditation	Thought protocol, cognitive distortions	Self-exploration, body exposure
4	Mindfulness towards thoughts	Situational analysis	Self-exploration with touch
5	Being present during sexual activity	Vertical arrow technique	Self-exploration with touch
6	Letting go	Cognitive restructuring	Sensate focus exercises
7	Detached awareness	Cognitive restructuring	Sensate focus exercises
8	Addressing difficulties	Working with cognitive methods after the intervention	Summary of Modules 1-7

#### COPE Program (I-CBT)

The focus of COPE are cognitive behavioral techniques that are commonly used in the treatment of mental health problems such as depression and anxiety. In Module 3, participants will learn about automatic thoughts and cognitive distortions [41] and will receive information about the relationship between cognitions, emotions, and behavior. Participants will be asked to identify their automatic thoughts about sexuality, sexual desire, and sexual relationships and will be encouraged to pinpoint underlying thought distortions. In Modules 3 and 4, participants will learn about situational analysis [42,43], and will be guided to apply this method to a personal situation relevant to their low desire (eg, declining a partner’s sexual initiative). Situational analysis can be used to improve understanding of the bidirectional relationship between inner experiences (ie, thoughts and feelings) and overt behavior (ie, what someone does or says) in interpersonal situations. It can be a means to identify problematic thought and behavior patterns and encourages individuals to think about strategies for more positive outcomes in future situations. In Module 5, participants will be introduced to the concept of maladaptive cognitive schemas. They will learn about underlying processes and the way in which schemas develop over the lifespan. They will be asked to identify their own negative concepts related to low sexual desire using the downward arrow technique [41]. Building on content of previous modules, challenging schemas and developing alternative thoughts will part of Modules 6 and 7.

#### MIND Program (I-MBT)

MIND focusses on mindfulness as a therapeutic concept and covers several formal and informal mindfulness-based exercises (eg, body scan, sitting meditation, or mindful eating) adapted from established mindfulness treatments for chronic depression, stress [44], and sexual dysfunctions [45]. Every module starts with a short mindfulness exercises, a so-called Check-In, that invites participants to mindfully focus on different targets such as the breath, negative thoughts, or bodily sensations. In Module 1, participants will learn about the concept of mindfulness in general and will learn about formal mindfulness exercises. In Module 2, they will be introduced to informal mindfulness exercises and breathing meditation. In Module 3, participants will learn detachment from negative thoughts and bodily sensations, as well as acceptance of negative thoughts and emotions. With the progressing mindfulness practice, participants will be encouraged to focus on detachment from all bodily, cognitive, and emotional experiences (Modules 4-6). In Modules 7 and 8, participants will be enabled to consolidate the newly acquired skills into an everyday mindfulness practice.

#### Treatment Platform

The technology platform used to deliver the interventions is provided by Minddistrict. This company is responsible for the provision and maintenance of the platform. Its content management system is used to upload the interventions, add new participants, and eCoaches. Access to the platform is provided by a combination of email and personalized password. The platform conforms to all required quality standards and operates according to the ISO 27000 and NEN 7510 norms. All data are securely stored on ISO 27000-certified servers and transmitted using HTTPS with SSL certificates (AES-256 and SHA-1, 2048-bit RSA).

#### Module Format

Each module is built as a series of webpages with each page featuring text-based information, illustrations, audio, or video clips. Three case vignettes are revisited throughout the interventions to provide examples of how different women may benefit from particular aspects of the treatments and how difficulties with certain exercises can be overcome. Additional content (eg, summary of scientific findings) can be accessed by participants who are interested to learn more about a certain topic. Each module is introduced by a summary of the previous content and an overview of the content to follow. A list of all at-home exercises and a short overview of the completed module are provided at the end of all modules. All worksheets and audio files included in the interventions can be accessed over the platform itself. In addition, participants can access study materials via a link to an external online hosting service.

#### Coaching

eCoaches are female graduate psychology students, specifically trained for the study and supervised by the study coordinator (MM). eCoaches are informed as soon as a participant that is allocated to their account has completed a module. Within the next 48 hours, they provide an individual feedback based on the participants’ answers. To increase comparability between eCoaches, they follow guidelines previously outlined for the coaching process. These guidelines were developed based on the existing literature [46,47] and aim to enable eCoaches to establish a therapeutic alliance and a productive therapeutic working environment. Feedback should include empathetic reassurance, unconditional positive regard, guidance on exercises, and encouragement of openness to new experiences. All eCoaches will be supervised by the study coordinator (MM), a clinical psychologist.

### Measures

#### Primary Outcome

The primary outcome is sexual desire, as measured by the Sexual Interest and Desire Inventory-Female (SIDI-F) [48]. The SIDI-F is a 13-item assessment tool validated for use with clinical populations. The item domains assess frequency and intensity of sexual desire and arousal over the past month [49]. An adapted self-report version, called SIDI-F-SR, will be used to assess sexual desire at all assessment points. This self-report scale has been used in studies with women with distressing low sexual desire [17,50] and was found to have good internal consistency. The SIDI-F-SR has shown high agreement with the SIDI-F (ICC 0.86) in a subsample (n=170) of this study. When corrections for the restriction of range were applied, internal consistency of the SIDI-F-SR was 0.91. Test–retest reliability over a period of 14 weeks was good (*r*=0.74) [51].

#### Secondary Outcome

The Female Sexual Distress Scale Revised (FSDS-R) [52] is a validated 13-item measure used extensively in treatment outcome studies [53], with 1 item specifically assessing sex-related distress due to low sexual desire. The FSDS-R covers the frequency of negative cognitions or emotions women experience with regard to their sexual life overall, sexual problems, or sexual relationships. Items are rated on a 5-point Likert-scale (never to always), resulting in a total score ranging from 0-52. Higher scores indicate higher levels of distress. In previous studies, the FSDS-R has displayed good discriminant validity, high test–retest reliability, and high internal consistency [52].

#### Other Measures

Other measures will comprise sociodemographic variables (eg, age, education, relationship status, and duration), symptom checklists, and a standardized clinical interview for diagnoses according to DSM-5 [54,55]. For an overview of measures, see Table 2. Relationship satisfaction will be assessed with the Relationship Assessment Scale [56]. Sexual communication will be assessed with the Dyadic Sexual Communication Scale [57,58] and mindfulness, body image, and body connection will be assessed by the Mindful Attention and Awareness Scale [59], Body Image Self-Consciousness Scale [60], and the Scale of Body Connection [61], respectively. Possible adverse effects of the interventions will be assessed with the Inventory for the Assessment of Negative Effects of Psychotherapy [62]. Experiences with traumatic events or childhood abuse will be assessed with a subsection of the Childhood Trauma Questionnaire [63-65]. Levels of depression and general anxiety will be measured by the Patient Health Questionnaire 9 [66] and the Generalized Anxiety Disorder 7 [67], respectively. Sexual excitation and sexual inhibition will be assessed with a short version of the Sexual Inhibition/Sexual Excitation Scales [68,69]. Compassionate attitude toward one self will be measured by the Self-Compassion Scale [70]. The level of involvement with thoughts about sexuality will be assessed by the Rumination subscale of the Rumination-Reflection Questionnaire [71,72]. Reasons for drop-out, help-seeking behavior, and reasons for nonutilization of health care for sexual problems will be measured with self-developed items. The relationship between eCoach and participant will be measured with the Helping Alliance Questionnaire [73], whereas overall satisfaction with the program will be measured with an adapted version of the Client Satisfaction Questionnaire [74].

**Table 2 table2:** Overview of measures.

Measure		Timepoint					
		T0	T1	T2	T3	T4	T5
Sexual Interest and Desire Inventory-Female (self-report version: SIDI-F-SR)		—^a^	X	X	X	X	X
Female Sexual Distress Scale Revised		—	X	X	X	X	X
**Other measures (in alphabetical order)**							
	Body Image Self-Consciousness Scale	—	X	—	X	X	X
	Childhood Trauma Questionnaire (Subscales for Sexual, Physical, and Emotional Abuse)	X	X	—	—	—	—
	Client Satisfaction Questionnaire adapted to internet-based interventions (CSQ-I)	—	—	X	X	—	X
	Diagnosis checklist for sexual dysfunctions (ICD-10^b^ and DSM-5^c^)	X	—	—	—	—	—
	Dyadic Sexual Communication Scale	—	X	—	X	X	X
	Generalized Anxiety Disorder 7	—	X	—	X	X	X
	Inventory for the Assessment of Negative Effects of Psychotherapy	—	—	—	X	X	X
	Mindful Attention and Awareness Scale	—	X	—	X	X	X
	Patient Health Questionnaire 9	—	X	—	X	X	X
	Potential reasons for dropout	—	—	—	X	X	X
	Relationship Assessment Scale	—	X	—	X	X	X
	Rumination-Reflection Questionnaire	—	X	—	X	X	X
	Scale of Body Connection	—	X	—	X	X	X
	Self-Compassion Scale	—	X	—	X	X	X
	Sexual Inhibition/Sexual Excitation Scales (short version)	—	X	—	X	X	X
	Sociodemographic questionnaire	X	X	—	X	X	X
	Utilization of additional help	—	—	—	X	X	X

^a^Dashes indicate that the measure will not be assessed.

^b^ICD-10: tenth edition of the International Classification of Diseases.

^c^DSM: fifth edition of the Diagnostic and Statistical Manual of Mental Disorders.

#### Qualitative Interviews

To gain insights into idiosyncratic factors influencing adherence and acceptance of COPE and MIND, structured telephone interviews will be conducted. Twelve weeks after randomization, participants in active conditions who have accessed at least four modules will be invited to take part in the interview until 25 interviews per active condition are completed. The interview questions cover topics such as experiences with the program, perceived changes and improvements, and their view on helpfulness of the coaching (see Multimedia Appendix 1 for a list of interview questions). Interviews will be conducted by trained graduate psychology students not involved in the eCoaching of the respective participant or the study coordinator (MM).

#### Experimental Tasks

To assess the impact of the interventions on sexuality-related interpretations and associations, participants will be asked to complete 2 reaction-time paradigms at T1 and T3. To complete these paradigms, they will be asked to download a small computer program (ie, Inquisit 5 Web App) to their computer. Instructions on how to install the program will be provided in an email and on the download website. Sexuality-related associations will be assessed with a STIAT, an experimental task prompting participants to categorize stimuli into different categories as quickly as possible [75,76]. Reaction times are used as a behavioral reference toward the presented stimuli material. The underlying assumption of the task is that strongly associated stimuli are processed more quickly compared to weakly associated stimuli, as reflected in participants’ categorization speed (eg, faster reaction times when sexual pictures are paired with the category "I don't want" as compared to "I want"). Sexuality-related interpretations will be assessed with an SST that requires participants to sort 6 words presented on a computer screen (eg, “desire I sexual often feel seldom”) into a grammatically correct sentence, using only 5 words [77,78]. Depending on the omitted word, the resulting sentence can have a positive (eg, “I often feel sexual desire”) or negative valence (eg, “I seldom feel sexual desire”). A study using a convenience sample of women with mixed levels of sexual desire suggested that lower levels of desire are associated with more negative sentences in the SST [79].

### Statistical Analyses

Analyses will be conducted and reported according to the CONSORT guidelines [30]. An intention-to-treat approach will be employed to analyze data. Missing data will be handled using multiple imputations [80]. In addition, study completer analyses including only participants who completed data assessments and intervention completer analyses including only participants who completed all treatment modules will be conducted. Differences in the primary and secondary outcomes between each of the active conditions (ie, I-CBT and I-MBT) and the waitlist control group will be examined with repeated measures ANOVA, and standardized effect sizes (Cohen *d*) and their respective confidence intervals will be calculated for comparison. Predictors and moderators of change will be analyzed via structural equation modeling on an exploratory basis. For statistical analyses, the significance level will be set at *P*<.05, 2-sided, or *P*<.025, 2-sided, in cases where 2 parallel analyses for each of the active conditions are conducted.

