### Study Aim

The aim of this study is to present the protocol of a randomized controlled trial (RCT) comparing 2 internet-based interventions for low sexual desire in women with HSDD to a waitlist. Hypotheses 1 and 2 are that at posttreatment (12 weeks after randomization), women receiving I-CBT or I-MBT report significantly more sexual desire (primary outcome; H1) and less sexuality-related distress (secondary outcome; H2) compared to a waitlist control condition. It is also proposed that these differences are maintained at the 6- and 12-month follow-up assessments. Differences in outcomes between I-CBT and I-MBT at the 12-week-, 6-month, and 12-month assessments are inspected on an exploratory basis. It is also explored whether improvements from pretreatment to posttreatment are dependent on treatment dosage (eg, completed modules, time spent with at-home exercises) and whether changes in proximal variables such as mindfulness or rumination mediate improvement in symptoms in either one of the treatments. Whether improvements in symptoms are predicted by changes in sexuality-related interpretations and associations assessed with computerized reaction-time paradigms (ie, Single-Target Implicit Association Test [STIAT] and Scrambled Sentences Task [SST]) is examined as well. To explore participants’ perceptions of the treatments more thoroughly, qualitative telephone interviews will be conducted with 25 participants in the I-CBT and I-MBT condition, respectively.

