## Methods

### Design

The study is an RCT of 2 internet-based treatments (ie, I-CBT and I-MBT) versus a waitlist control group. Analyses will be conducted and reported in accordance with the statement by Consolidated Standards of Reporting Trials (CONSORT) [30]. Recommendations for the reporting of psychological and eHealth interventions will be considered [31,32]. This 3-arm superiority trial with 2:2:1 allocation ratio will demonstrate whether the benefit from I-CBT or I-MBT is superior to natural remission of low desire symptoms. Outcomes will be assessed at baseline (T1), at midtreatment (T2, 5 weeks after randomization, only in active conditions), at posttreatment (T3, 12 weeks after randomization), and at 6 months (T4) and 12 months (T5) after randomization. Two computerized reaction-time paradigms will be administered at T1 and T3. Participants will receive up to 3 reminders for each assessment (after 7, 14, and 21 days). Qualitative telephone interviews with active participants will be conducted at T3. For an overview of participant flow, see Figure 1.

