#### Randomization

Enrolled participants will be randomly assigned to 1 of the 3 conditions. To maximize the power of the study to detect differences between active and control conditions, quotas are applied to allocate 40% of participants to each of the active treatments and 20% to the waitlist. A stratification procedure will be applied to balance relationship status (partner vs no partner) and age (younger than 30 years vs 31 years and older). These variables were selected based on their known effect on sexual desire [34-36]. An internet-based randomization tool will be used by a trained research assistant not involved in the recruitment, screening, or treatment of participants [37]. The clinical psychologist conducting the diagnostic interviews will not be involved in the randomization process but will be informed about the assigned condition after its completion. Block randomization with varying block-sizes will be applied. Participants will be informed about their assigned condition. Participants in the active conditions will gain immediate access to the respective program. Participants assigned to waitlist will receive access to a program of their choice (ie, I-CBT or I-MBT) 6 months after randomization.

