### Power Analysis

Sample size was determined based on an a priori power analysis and practical considerations. Psychological therapies for sexual dysfunctions in women yield large effects for symptom improvement compared to waitlist controls (*d*≈0.9) [15,29]. To use a conservative estimate, a medium effect of *d*=0.6 was expected for both active conditions compared to the waitlist (unpaired *t* test two-sided, α=.025, 1–β=80%, allocation rate 2/1). In addition, a postsample of 81 women for each of the 2 active conditions would yield statistical power of 60%, 71%, and 81% to detect differences of *d*=0.35, 0.40, or 0.45, respectively. Although this study is not sufficiently powered to detect smaller differences in efficacy between I-CBT and I-MBT, it will still provide first estimates that may be useful for future studies. As internet-based interventions commonly suffer from relatively high attrition rates, a 30% loss at postassessment analysis is expected. Based on these considerations, a total of 266 women will be enrolled in the study.

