## Results

Recruitment has begun in January 2019 and is expected to be completed in August 2021. Results will be published in 2022. We anticipate improvements in our primary (ie, sexual desire as measured with the SIDI-F-SR) and secondary outcomes (ie, sexual distress as measured with the FSDS-R) from pretreatment to posttreatment in the I-CBT and I-MBT conditions compared to the waitlist. These improvements are expected to be sustained at 6- and 12-month follow-up. No significant difference in outcomes between active conditions is expected. However, potential differences in efficacy between active conditions will be explored, and the trial will be sufficiently powered to identify medium to large differences between I-CBT and I-MBT.

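### The named primary model, repeated measures ANOVA, is less precise than a baseline-adjusted analysis and has no stated visits or 12-week contrast

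*Protocol article*

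**What the plan says.** All references are to the protocol article.

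- **Statistical Analyses** names one model for the primary outcome (SIDI-F-SR) and the secondary outcome (FSDS-R): differences between each active arm and "the waitlist control group will be examined with repeated measures ANOVA". Two-sided P<.025 applies ("2-sided, in cases where 2 parallel analyses for each of the active conditions are conducted"). No visits, model term, contrast or covariate is given.
- **Study Aim** places the primary hypothesis at one time point: "at posttreatment (12 weeks after randomization), women receiving I-CBT or I-MBT report significantly more sexual desire (primary outcome; H1". Maintenance at 6 and 12 months is proposed in addition.
- **Results** words the expected effect as improvement "from pretreatment to posttreatment in the I-CBT and I-MBT conditions compared to the waitlist".
- **Power Analysis** sizes the trial on an unpaired t test with d=0.6 ("two-sided, α=.025, 1–β=80%, allocation rate 2/1").
- **Randomization**: "A stratification procedure will be applied to balance relationship status (partner vs no partner) and age". The stated reason is that both are known to affect sexual desire. Neither is mentioned again under Statistical Analyses. The same section gives the waitlist program access from 6 months.
- **Design** has an assessment "at midtreatment (T2, 5 weeks after randomization, only in active conditions".
- **Primary Outcome**: "Test–retest reliability over a period of 14 weeks was good", with r=0.74.

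**The concern.** Repeated measures ANOVA offers several tests, and the article does not say which one decides the trial. Two things are at stake.

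The first is precision. The baseline score enters the ANOVA as a repeated level of the outcome, not as a covariate. On two visits this gives a change-score test. Regression on baseline does better with the same data, and the stratification factors are already recorded for every woman.

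The second is the target. H1 concerns week 12. If T4 or T5 also enter the ANOVA, a significant omnibus group-by-time interaction no longer says that the arms differ at week 12. The visit schedule fits a single ANOVA poorly in any case: T2 has no waitlist data, and T5 falls after the waitlist has gained program access.

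**Working it through.** **Inputs**
- From Power Analysis: d=0.6, two-sided α=.025, 2:1 per comparison, 30% loss, 266 enrolled.
- From Design: overall allocation 2:2:1.
- From Primary Outcome: r=0.74 over 14 weeks, used as a proxy for the correlation between baseline and week 12.
- Assumed: r=0.4 and 0.5 as a lower range, equal variances at both visits, and the same r in both arms.

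**Step 1. The plan's own figure.** An unpaired t test with 81 active and 41 waitlist women, d=0.6 and α=.025 has 80.4% power (noncentral t). This agrees with the 81 per active arm in Power Analysis.

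**Step 2. Women left at week 12.** 266 × 0.4 × 0.7 = 74.5 per active arm and 266 × 0.2 × 0.7 = 37.2 on the waitlist. I use 74 and 37.

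**Step 3. Variance of the 12-week contrast, relative to a t test on week 12 alone**
- Group-by-time on T1 and T3 (change score): 2(1−r)
- ANCOVA on baseline: 1−r²
- Ratio of ANCOVA to change score: (1−r²) / [2(1−r)] = (1+r)/2, which is below 1 whenever r is below 1.

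**Step 4. Power.** The noncentrality is 0.6 × √(74×37/111) / √(variance factor) = 2.980 / √(variance factor).

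| r | Change-score factor | ANCOVA factor | Ratio | Power, change score | Power, ANCOVA |
|---|---|---|---|---|---|
| 0.74 | 0.52 | 0.452 | 0.87 | 96.7% | 98.4% |
| 0.5 | 1.00 | 0.75 | 0.75 | 75.9% | 87.7% |
| 0.4 | 1.20 | 0.84 | 0.70 | 67.3% | 83.5% |

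The t test on week 12 alone has 75.9% power with these numbers. The change-score test beats it only when r exceeds 0.5. ANCOVA beats it at any r above 0.

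**Step 5. If T4 also enters the ANOVA.** Take between-arm differences of 0, 0 and 0.6 at T1, T3 and T4, so that there is no effect at week 12. The sum of squares about their mean of 0.2 is 0.04 + 0.04 + 0.16 = 0.24. Under compound symmetry the omnibus noncentrality is (74×37/111) × 0.24 / (1−r) = 5.92 / (1−r), with 2 and 218 degrees of freedom. It is 9.87 at r=0.4 and 22.8 at r=0.74, and the test rejects with probability 72% and 98%. A significant omnibus interaction over these visits would therefore not establish H1.

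**Step 6. Stratification factors.** Their correlation with the outcome, given baseline, is not stated, so the gain from including them cannot be calculated.

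**The case against.** The strongest reply is that the article is a condensed account. It is silent on covariates, visits and contrasts but does not rule them out, and such detail may stand in a full protocol or SAP that is not shown. This stands for the missing detail alone. It does not cover the choice of model, which the article states and which can be compared with a better one.

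A reader might infer that the planned model cannot test H1. The documents do not support that. The expected effect in Results is a pretreatment-to-posttreatment change against waitlist. This is the T1/T3 group-by-time term, and under randomisation it estimates the same 12-week difference as ANCOVA. The difficulty in Step 5 arises only if further visits enter.

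A reader might also point to the low power of the group main effect, which averages in the pre-randomisation score. The article never names that effect as the primary test, so its power is not relevant here.

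Nor can one say in general that the gain makes up for the sample size shortfall. On the planned t test, 30% loss from 266 leaves 75.9% power, 4.1 points below 80%. At r=0.74, moving from change score to ANCOVA gains 98.4 − 96.7 = 1.7 points, and the change-score test is already well above 80%. The gain exceeds 4.1 points at the assumed r of 0.5 (11.8 points) and 0.4 (16.2 points), but the documents give no evidence for those values.

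On stratification, the factors are said to affect the level of desire, and a change score already removes stable differences in level. Leaving them out makes the standard errors conservative at worst, so validity is not threatened.

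**Conclusion.** The point holds as a low-cost improvement to a valid but less efficient and incompletely fixed analysis. On the favourable reading (T1 and T3 only), ANCOVA reduces variance by 13% at the article's r=0.74, worth under 2 power points. The reduction is 25 to 30% at an assumed r of 0.4 to 0.5, worth about 12 to 16 points. The direction holds at every r below 1; the size depends on r. The retest value is only a proxy, and the correlation could be lower if women respond differently to treatment. The power figures treat the 70% expected to be assessed as the available information and do not model multiple imputation.

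On the less favourable reading (more visits in one ANOVA), the omnibus interaction does not isolate week 12, T2 cannot enter a comparison with the waitlist, and T5 no longer compares with a waitlist without program access. The article does not say which reading applies. The benefit of including the stratification factors is plausible from the protocol's own rationale but cannot be quantified.

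**What to change.** Replace the ANOVA sentence in Statistical Analyses with wording to this effect:

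- SIDI-F-SR, and likewise FSDS-R, is analysed in each imputed dataset by ANCOVA at T3, or by a mixed model for T3, T4 and T5 with arm, visit and arm-by-visit. Either model includes the baseline score, relationship status and age stratum.
- The primary tests are the I-CBT minus waitlist and I-MBT minus waitlist contrasts in SIDI-F-SR at T3, each at two-sided .025.
- T2 does not enter any comparison with the waitlist.
- T4 and T5 are secondary contrasts, reported with a note that the waitlist has program access from 6 months.

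No new data are needed: both scales are measured at T1, and both stratification factors are known at randomisation. The cost is a change of wording. Because recruitment began in January 2019, it should be made as a dated amendment before outcomes are compared between arms.

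### Optional improvement: the valid fixed .025 level for the two active-versus-waitlist tests could be replaced by Holm, which has at least as much power at the same .05 family-wise level

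*Protocol article*

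**What the plan says.** The Statistical Analyses section sets .05 two-sided as the general level and lowers it to .025, "2-sided, in cases where 2 parallel analyses for each of the active conditions are conducted". It names no step-down, hierarchical or Dunnett-type rule. It promises Cohen d with confidence intervals but gives no interval level.

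The Power Analysis section uses the same level for an unpaired two-sided t test: "α=.025, 1–β=80%, allocation rate 2/1". The effect is d=0.6, which "was expected for both active conditions compared to the waitlist". The section also refers to "a postsample of 81 women for each of the 2 active conditions". It states that "a 30% loss at postassessment analysis is expected" and that "a total of 266 women will be enrolled in the study".

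The Design section describes "This 3-arm superiority trial with 2:2:1 allocation ratio". Under Study Aim, H1 (sexual desire) and H2 (sexuality-related distress) each cover both programmes against waitlist at 12 weeks. The Results section anticipates improvement in both.

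**The concern.** The trial wants a conclusion on each programme and expects both to work. Under the fixed split, a programme with a P value between .025 and .05 is declared unproven even when the other programme has already succeeded. Once one null hypothesis has been rejected, only one remains, and it can be tested at the full .05 without exceeding the family-wise limit. The fixed rule leaves that part of the error allowance unused. What is at stake is the chance of missing the second of two effective programmes. The validity of any claim the trial makes is not at stake.

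**Working it through.** **Inputs from the protocol article.** Two-sided α=.025 per test, power 80%, active:waitlist 2:1, d=0.6 in both arms, 81 analysed per active arm, 266 enrolled, 30% loss, allocation 2:2:1. The analysed waitlist size is not stated; 2:1 implies about 41.

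**The plan's own figure.** For an unpaired t test, the noncentrality is d/√(1/n₁+1/n₂) = 0.6/√(1/41+1/81) = 3.13 on 120 degrees of freedom. The exact noncentral t power at two-sided .025 is 80.4%, so the stated 80% reproduces.

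**Sample if 30% of 266 are lost.** 266 × 0.70 = 186.2. Split 2:2:1 this is 74.5, 74.5 and 37.2, taken as 74/74/37.

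**Correlation of the two tests.** With n on waitlist and 2n per active arm, each contrast has variance σ²(1/n + 1/2n) = 1.5σ²/n. The covariance through the shared waitlist is σ²/n. The correlation is 1/1.5 = 2/3.

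**Rules compared.** Fixed: reject each hypothesis if its P<.025. Holm: reject the smaller P if <.025 and, if it is rejected, reject the other if <.05. Simulation, 1,000,000 trials per scenario, pairwise t tests sharing one waitlist arm.

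| Analysed | d (two arms) | Quantity | Fixed .025 | Holm |
|---|---|---|---|---|
| 81/81/41 | 0.6, 0.6 | per arm | 80.5% | 84.7% |
| | | both | 71.3% | 79.8% |
| | | at least one | 89.7% | 89.7% |
| 74/74/37 | 0.6, 0.6 | per arm | 76.0% | 80.6% |
| | | both | 65.5% | 74.9% |
| | | at least one | 86.4% | 86.4% |
| 81/81/41 | 0.9, 0.9 | both | 98.6% | 99.3% |
| 74/74/37 | 0.9, 0.9 | both | 97.4% | 98.7% |

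**Error rates.** With no effect in either arm, the chance of any false positive is 4.4% under both rules at both sample sizes. With one effective and one ineffective arm, the false-positive rate for the ineffective arm is:

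| Analysed | Effective arm d | Fixed .025 | Holm |
|---|---|---|---|
| 74/74/37 | 0.6 | 2.5% | 4.0% |
| 74/74/37 | 0.9 | 2.5% | 4.8% |
| 81/81/41 | 0.6 | 2.5% | 4.1% |
| 81/81/41 | 0.9 | 2.5% | 4.9% |

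**Sensitivity to the planned analysis.** The plan is repeated measures ANOVA, not a post-score t test. Suppose that d=0.6 is in raw-score SD units and that the pre-post correlation is r (both assumptions). The effect on the change score is then 0.6/√(2(1−r)). The Primary Outcome section gives a 14-week test-retest r of 0.74. At 74/74/37:

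| r | Effect on change | Both: fixed → Holm | Per arm: fixed → Holm |
|---|---|---|---|
| 0.50 | 0.60 | 65.5% → 74.8% | 75.9% → 80.6% |
| 0.60 | 0.67 | 77.8% → 85.1% | 85.3% → 89.0% |
| 0.74 | 0.83 | 94.6% → 97.0% | 96.8% → 98.0% |

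The gain for both arms therefore runs from about 9 points at r=0.50 to about 2.5 points at r=0.74.

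**The case against.** The strongest reply is that nothing here is wrong. The fixed split is valid, agrees with the sizing, and its cost was already paid in the sample size: at 81 and 41 analysed, the planned 80% is met. That stands, and the point is therefore only an improvement.

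Three stronger readings are tempting, and the document supports none of them.

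- A reader might infer that the fixed rule buys nothing in error control. It does buy something: an ineffective programme tested beside an effective one has a 2.5% false-positive rate, against 4.0% to 4.9% under Holm. Both respect the .05 family-wise limit, but the fixed rule is the stricter one.
- A reader might link the split to a power shortfall. Power of 76% per comparison at 74/74/37 arises from how 30% loss relates to an enrolment of 266. That is a separate matter and does not make this one weightier.
- A reader might take the 9-point gain as what the trial would obtain. It belongs to a post-score t test at d=0.6. The planned analysis may be more sensitive, and the Power Analysis section itself cites effects near 0.9. Either would shrink the gain.

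Two practical objections also stand. With intervals at 97.5%, the fixed rule can be matched exactly, whereas a second-step Holm success with P between .025 and .05 would have a 97.5% interval that includes zero. And recruitment began in January 2019, so relaxing a published significance rule needs a documented amendment.

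**Conclusion.** The point holds as a cheap improvement. Holm is never less powerful than the fixed .025 rule and keeps family-wise error at or below .05 under any dependence between the tests. That ordering depends only on the P values, so it carries over to the repeated measures analysis. With d=0.6 in both arms and a post-score t test, per-arm power rises by 4 to 5 points and power to show both by 8 to 9 points. Power for at least one arm does not change. The gain for both arms is about 2.5 points (about 1 point per arm) if r is near 0.74, and 0.7 to 1.3 points at d=0.9. The implied waitlist numbers, the use of r=0.74 for the pre-post correlation and the raw-score reading of d are assumptions. The present rule may properly be kept if the sponsor prefers the stricter per-programme error rate and intervals that can match the test decisions.

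**What to change.** In the Statistical Analyses section, replace the fixed .025 rule for these comparisons with: *For each of SIDI-F-SR and FSDS-R at T3, the two active-versus-waitlist tests use the Holm procedure: the smaller P value at .025 and, if significant, the other at .05 (two-sided, family-wise .05).*

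State the confidence interval level, for example 97.5%, and note that these intervals may not match a second-step decision.

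Record the change as a dated amendment before outcome data are analysed.

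The cost is a short text change plus the amendment. Sample size, assessments and participant burden are unaffected, and sizing at .025 remains valid because Holm's first step uses that level. The statistical price is the higher false-positive rate for a single ineffective arm, within the .05 limit.
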